# Early-stage squamous cell carcinoma of the oropharynx: Radiotherapy vs. Trans-Oral Robotic Surgery (ORATOR) – study protocol for a randomized phase II trial

**DOI:** 10.1186/1471-2407-13-133

**Published:** 2013-03-20

**Keywords:** Head and neck cancer, Oropharynx, Human papillomavirus, Radiotherapy, Transoral robotic surgery, Quality of life, Survival, Randomized controlled trial

## Abstract

**Background:**

The incidence of oropharyngeal squamous cell carcinoma (OPSCC) has markedly increased over the last three decades due to newly found associations with human papillomavirus (HPV) infection. Primary radiotherapy (RT) is the treatment of choice for OPSCC at most centers, and over the last decade, the addition of concurrent chemotherapy has led to a significant improvement in survival, but at the cost of increased acute and late toxicity. Transoral robotic surgery (TORS) has emerged as a promising alternative treatment, with preliminary case series demonstrating encouraging oncologic, functional, and quality of life (QOL) outcomes. However, comparisons of TORS and RT in a non-randomized fashion are susceptible to bias. The goal of this randomized phase II study is to compare QOL, functional outcomes, toxicity profiles, and survival following primary RT (± chemotherapy) vs. TORS (± adjuvant [chemo] RT) in patients with OPSCC.

**Methods/Design:**

The target patient population comprises OPSCC patients who would be unlikely to require chemotherapy post-resection: Tumor stage T1-T2 with likely negative margins at surgery; Nodal stage N0-2, ≤3 cm in size, with no evidence of extranodal extension on imaging. Participants will be randomized in a 1:1 ratio between Arm 1 (RT ± chemotherapy) and Arm 2 (TORS ± adjuvant [chemo] RT). In Arm 1, patients with N0 disease will receive RT alone, whereas N1-2 patients will receive concurrent chemoradiation. In Arm 2, patients will undergo TORS along with selective neck dissections, which may be staged. Pathologic high-risk features will be used to determine the requirement for adjuvant radiotherapy +/- chemotherapy. The primary endpoint is QOL score using the M.D. Anderson Dysphagia Inventory (MDADI), with secondary endpoints including survival, toxicity, other QOL outcomes, and swallowing function. A sample of 68 patients is required.

**Discussion:**

This study, if successful, will provide a much-needed randomized comparison of the conventional strategy of primary RT vs. the novel strategy of primary TORS. The trial is designed to provide a definitive QOL comparison between the two arms, and to inform the design of an eventual phase III trial for survival outcomes.

**Trial registration:**

NCT01590355

## Background

The incidence of oropharyngeal squamous cell carcinoma (OPSCC) is rapidly increasing, associated with rising rates of oral infection with the human papillomavirus (HPV) [1]. Patients with HPV-related cancers tend to present at a younger age and experience markedly improved survival, compared to patients with smoking- and alcohol-related head and neck cancers [1]. In such young patients with good prognosis, survivorship is of paramount importance, as they are likely to survive their cancer and may have to cope with the side effects of therapy and secondary disability for decades. Optimizing post-treatment quality of life (QOL) for patients with OPSCC has become one of the most important issues in head and neck oncology.

Historically, oropharyngeal cancer was frequently managed with open surgery, with or without postoperative radiotherapy (RT). Although this approach was reasonably effective at obtaining tumor control, the speech, swallowing and cosmetic outcomes were poor. Surgical access of the oropharynx traditionally involves large facial and neck incisions that interrupted critical neurovascular and muscular structures [2]. This resulted in high complication rates, leading many centers to move towards organ preservation approaches utilizing radiation as primary treatment with surgery reserved for salvage [3]. Although a randomized trial was never carried out comparing surgery and RT, a meta-analysis of observational studies demonstrated that primary surgery and primary RT approaches were equivalent in terms of survival, but major complications of therapy were markedly worse in the primary surgery patients [2].

For patients with high-risk cancers of the oropharynx, concurrent cisplatin-based chemotherapy is delivered with RT and achieves a significant improvement in survival, compared to radiotherapy alone [4]. However, it is increasingly recognized that these improvements in survival come at the cost of increased acute and late toxicities: these include dysphagia, mucositis, xerostomia, fibrosis, osteoradionecrosis, neutropenia, neurotoxicity, nephrotoxicity and ototoxicity [5]. The addition of chemotherapy to RT increases the risk of long-term gastrostomy tube dependence from 1% to 13% [5]. These treatment-related toxicities can significantly affect QOL.

These toxicity risks, and their consequent reduction in QOL, have led to increasing interest in minimally invasive surgical approaches for OPSCC, especially transoral robotic surgery (TORS) using a surgical robot. The surgical robot is comprised of a binocular endoscope and two low profile articulating arms that can be placed in the oropharynx, while the surgeon sits at a separate console to control the instruments. This allows the operating surgeon to overcome the visualization and access challenges that can otherwise make transoral surgery in this area challenging, if not impossible. The ability to avoid incisions in the face and neck, which were required prior to the implementation of the robot, preserves neuromuscular structures that are critical for speech and swallowing. Preliminary case series of TORS have reported encouraging oncologic, functional, and QOL outcomes compared with primary RT [6,7].

Outcomes after TORS have been summarized in a recent systematic review [6]. All reports involve prospective or retrospective single-arm case series with varying use of adjuvant therapy without adequate controls. This is in stark contrast to the large number of randomized controlled trials of chemoradiation (CRT) for OPSCC. Favourable gastrostomy tube rates (0–9.5% at one year and 0% at two years post treatment) have been reported following TORS [6]. In contrast, feeding tube rates in CRT series range from 9 to 39% at one year [8,9]. Patients undergoing TORS experience excellent 2-year disease free survival (DFS) and overall survival (OS) rates of 79% to 89% and 82% to 90%, respectively [6]. CRT trials report 3-year DFS and OS rates of 42% to 76.5% and 51% to 85%, respectively [8,9]. Two studies have explored the impact of TORS on QOL. Patients receiving TORS alone report better health-related QOL compared to individuals receiving TORS plus adjuvant radiation or chemoradiation [7]. Swallowing-related QOL is reported to decrease immediately following TORS intervention, but has been demonstrated to improve by one year post-treatment, with possible further improvement thereafter [10].

Although these data would appear to favor a surgical approach, a careful review of the literature reveals that this is a tremendously biased comparison. The TORS studies include a much smaller fraction of T3/T4 tumors (0–30%) and N3 neck disease (0–4%) compared with CRT series (31–86% T3/T4 and 2.5–12% N3) [6,8,9]. There are numerous additional confounders that make these comparisons invalid including: 1) patients receiving surgery have been carefully selected (i.e. ‘confounding by indication’, which cannot be adequately controlled for in observational studies [11]), 2) each study contains a different fraction of HPV-positive tumors, and 3) the majority of TORS patients receive adjuvant therapy including radiation (24%) or chemoradiation (54%) [12], making the true benefits of TORS unclear. Not surprisingly, management of OPSCC is now one of the most contentious and important issues in head and neck oncology practice in the wake of the growing HPV OPSCC epidemic.

Given the rapid treatment paradigm shift in the absence of level I evidence, the high cost of acquiring a surgical robot, and increasing numbers of affected patients due to the HPV epidemic, a randomized trial is critical to guide the optimal management of OPSCC. The goal of this randomized phase II study is to formally compare QOL in patients with oropharyngeal cancer (T1-2, N0-2) after TORS vs. primary RT, and to inform the design of a large, definitive, comparative phase III trial assessing survival.

## Methods/Design

This study has been approved by the Ontario Cancer Research Ethics Board (#12-006), in compliance with the Helsinki Declaration.

### Objectives

To compare QOL after primary radiotherapy [± chemotherapy] (Arm 1) vs. TORS [± adjuvant (chemo)radiotherapy] (Arm 2) in patients with squamous cell carcinoma of the oropharynx, to compare toxicity profiles, and to conduct a non-definitive comparison of survival between the two modalities. (See Figure 1 - Study Schema and Figure 2- Timeline of Interventions)

**Figure 1 F1:**
[figure not shown]
**Study schema. **HPV: human papilloma virus; quality of life: QOL.

**Figure 2 F2:**
[figure not shown]
Timeline of interventions.

#### Primary endpoint

• QOL 1-year post-treatment

 ○ Assessed with the MD Anderson Dysphagia Inventory (MDADI)

#### Secondary endpoints

• Overall Survival

 ○ Defined as time from randomization to death from any cause

• Progression-free survival

 ○ Time from randomization to disease progression at any site or death

• QOL at other time points

 ○ Using the MD Anderson Dysphagia Inventory (MDADI), the EORTC QLQ-C30 and H&N35 scales, the Voice Handicap Index (VHI-10), the Neck Dissection Impairment Index (NDII), and the Patient Neurotoxicity Questionnaire (PNQ).

• Toxicity

 ○ Assessed by the National Cancer Institute Common Toxicity Criteria (NCI-CTC) version 4

• Swallowing function, measured by:

 ○ Feeding tube rate at 1-year

 ○ MDADI

 ○ CTC-AE Dysphagia scores

#### Inclusion criteria

• Age 18 or older, providing informed consent

• ECOG performance status 0–2

• Histologically confirmed squamous cell carcinoma

• Primary tumor site in the oropharynx (includes tonsil, soft palate, base of tongue, walls of oropharynx)

• Tumor stage: T1 or T2, with likely negative resection margins at surgery

• Nodal stage: N0, N1 (≤ 3 cm), or N2 (between 1–3 cm, on either side of the neck), without extranodal extension on pre-randomization imaging.

• CBC/differential obtained within 4 weeks prior to randomization, with adequate bone marrow function, hepatic, and renal function, defined as: Hemoglobin > 80 g/L; Absolute neutrophil count >1.5 × 10^9^ /L, platelets > 100 × 10^9^/L; Bilirubin < 35 umol/L; AST or ALT < 3 × the upper limit of normal; serum creatinine < 130 umol/L or creatinine clearance ≥ 50 mL/min

• Patient assessed at head and neck multidisciplinary clinic (with assessment by radiation oncologist and surgeon) and presented at multidisciplinary tumor board prior to randomization.

#### Exclusion criteria

• Serious medical comorbidities or other contraindications to radiotherapy, chemotherapy or surgery

• Prior history of head and neck cancer within 5 years

• Prior head and neck radiation at any time

• Metastatic disease

• Inability to attend full course of radiotherapy or follow-up visits

• Prior invasive malignant disease unless disease-free for at least 5 years or more, with the exception of non-melanoma skin cancer

• Unable or unwilling to complete QoL questionnaires

• Pregnant or lactating women

#### Evaluation

The following evaluations are required:

• History and physical examination by a radiation oncologist and head and neck surgeon within 8 weeks prior to randomization, including laryngopharyngoscopy.

• Staging within 12 weeks prior to randomization:

 ○ Contrast-enhanced CT of the head, neck, and chest

or

 ○ MRI of the head and neck with CT of the chest

• Histological confirmation of squamous cell carcinoma

• p16 or HPV tumor status

• CBC/differential, hepatic and renal function testing within 4 weeks of randomization

• Pregnancy test for women of child-bearing age within 2 weeks of randomization

• Dental evaluation within 6 weeks of randomization

• Assessment of dysphagia using CTC-AE version 4 within 2 weeks of randomization

• Completion of QOL scoring within 2 weeks of randomization

• Blood sample for mutational and copy number variation analysis (see section) within 4 weeks of randomization

• Signing of consent within 2 weeks of randomization

• Audiogram before initiation of treatment

### Treatment plan

#### Arm 1: Radiotherapy

Intensity modulated radiotherapy (IMRT) will be used for all patients in this study. IMRT can be delivered using fixed-gantry techniques or rotational techniques (e.g. Tomotherapy or Volumetric Modulated Arc Therapy [VMAT]). Doses and fractionations are shown in Table 1.

**Table 1 T1:** Radiotherapy doses and fractionations

**Target volume**	**Radical-intent dose* (Arm 1)**	**Adjuvant dose (Arm 2)**
Gross tumor and nodes	70 Gy in 35 fractions over 7 weeks	N/A
Region of positive margins or extra-nodal extension	N/A	64 Gy in 30 fractions over 6 weeks
High-risk nodal areas (and operative bed in Arm 2)	63 Gy in 35 fractions over 7 weeks	60 Gy in 30 fractions over 6 weeks
Low-risk nodal areas	56 Gy in 35 fractions over 7 weeks	54 Gy in 30 fractions over 6 weeks

*In Arm 1, accelerated or hyperfractionated regimens may be used at the discretion of the radiation oncologist (e.g. same doses but delivered in 6 weeks).

### Immobilization and localization

All patients will be immobilized in a custom thermoplastic shell and will undergo a planning CT simulation encompassing the head and neck to below the clavicles. Contrast will be used (unless contra-indicated) for patients in Arm 1. For patients in both arms, the planning CT will be fused with other diagnostic imaging (e.g. MRI scans or pre-operative CT scans for patients in Arm 2) where necessary.

### Radiotherapy volume definitions

#### Arm 1

The gross tumor volume (GTV) is defined as the tumor and any nodes that are either: 1 cm or more in short axis, necrotic, PET positive (where applicable) or biopsy-proven to contain carcinoma. A 5 mm expansion will be added to create the clinical target volume (CTV) CTV70 (excluding natural boundaries of spread), with a further 5 mm to create the planning target volume (PTV) PTV70, which will be treated to a dose of 70 Gy in 35 fractions.

An optional high-risk nodal volume (CTV63) may be defined for areas of uncertainty (e.g. suspicious nodes not meeting the criteria above). A 5 mm margin will be added to create the PTV63, which will be treated to a dose of 63 Gy in 35 fractions.

A lower-risk nodal volume (CTV56) will be defined to include the standard lymphatic drainage sites. For well-lateralized, node-negative tonsillar primaries, this can be limited to the ipsilateral neck; for primaries at the tongue base, this must include both sides of the neck. For patients with a positive node, the contralateral neck must be treated. A 5 mm margin will be added to create the PTV56, which will be treated to a dose of 56 Gy in 35 fractions.

In Arm 1, accelerated or hyperfractionated regimens may be used at the discretion of the radiation oncologist (e.g. same doses but delivered in 6 weeks by delivering 5 twice-daily (BID) treatments, maximum one BID treatment per week)

#### Arm 2

The highest-risk volume (CTV64) will consist of regions of positive margins or extra-nodal extension. A 5 mm margin will be added to create the PTV64, which will be treated to a dose of 64 Gy in 30 fractions.

An intermediate-risk volume (CTV60) will be defined to include the entire tumor bed. CTV60 will also include the pathologically-positive neck. If both sides of the neck are pathologically positive, then both are treated to 60 Gy. A 5 mm margin will be added to create the PTV60, which will be treated to a dose of 60 Gy in 30 fractions.

A lower-risk nodal volume (CTV54) can be defined to include the standard lymphatic drainage sites that have not been dissected and/or low-risk dissected sites. For patients with a positive node, this will include the contralateral neck. A 5 mm margin will be added to create the PTV54, which will be treated to a dose of 54 Gy in 30 fractions.

### Dose constraints

Target dose constraints are shown in Additional file 1: Appendix 1, adapted from RTOG protocols 1016 (Arm 1) and 0920 (Arm 2) [13], and the NCIC-CTG HN6 protocol. Dose constraints are the same for both arms as the radiobiological conversion factor is small.

### Radiotherapy planning

Intensity modulated radiotherapy (IMRT) will be used for all patients in this study. IMRT can be delivered using fixed-gantry techniques or rotational techniques (e.g. Tomotherapy or Volumetric Modulated Arc Therapy [VMAT]). All plans will be normalized to ensure that 95% of each PTV is covered by 95% of the prescription dose for that volume. The maximum dose to PTV70 (Arm 1) and PTV64 (Arm 2) should not exceed 110% of the prescribed dose, and no volume >1 cc outside of these two PTVs should receive >105% of the prescription dose.

### Radiotherapy quality assurance

In order to ensure patient safety and effective treatment delivery, a robust quality assurance protocol is incorporated. The following requirements must be completed for each patient:

• Prior to treatment, each radiotherapy plan will be discussed at head and neck quality assurance (QA) rounds.

• All dose delivery for intensity-modulated plans (including arc-based treatments) will be verified with phantom measurements before treatment by physics staff.

• Cone-beam CT will be used to verify patient positioning immediately prior to treatment at minimum on a weekly basis, with orthogonal x-rays used on other days.

### Concurrent chemotherapy in arm 1

Patients with T1-T2N0 tumors will receive radiotherapy alone, and patients with T1-2 N1-2 tumors will receive radiotherapy with concurrent systemic therapy. Chemotherapy will consist of cisplatin 100 mg/m^2^ delivered every 3 weeks, in 3-week cycles. For patients who are deemed unfit for high dose cisplatin, the dose and/or schedule can be modified, or cetuximab or weekly carboplatin AUC 1.5 can be used, at the discretion of the medical oncologist.

### Salvage surgery in arm 1

Treatment response will be evaluated 8–10 weeks after completion of radiation therapy. For patients with residual nodes > 1 cm in size, a salvage neck dissection will be done. For patients with relapse or progressive disease at any time subsequent to radiation treatment, surgical salvage will be offered if feasible.

### Arm 2: TORS

#### TORS for the primary tumor

For patients with easily accessible oropharyngeal tumors as determined by the consulting surgeon, they will proceed directly to transoral robotic surgery. For patients where adequate transoral access is in question, they will first undergo an examination under anesthesia prior to randomization to ensure adequate exposure can be obtained.

TORS will be carried out using the da Vinci surgical robot (Intuitive Surgical, Sunnyvale, CA, USA). The spatula cautery will be used to remove the tumors with 1 cm margins. At the time of surgery circumferential margins will be taken and sent for frozen section analysis. The resection will proceed until negative margins are obtained if feasible. The learning curve for surgeons carrying out TORS resections has been demonstrated to be short for early-stage cases, likely fewer than 10 cases, with improvements in operative time (but not oncologic outcomes) evident as learning occurs [14]. As a result, surgeons will be required to have carried out at least 10 TORS operations prior to enrolling patients on this trial. If a positive or close margin is found on the final pathology from the TORS resection, an attempt to clear the margin transorally may be performed within four weeks of the original TORS resection. This can be done with or without the robot at the surgeon’s discretion.

### Neck dissection

Patients will undergo standard selective neck dissections for the lymph node areas at risk at the time of TORS, or as a staged procedure within three weeks of the primary site resection, at the discretion of the surgeon. Patients with tonsillar, lateral pharyngeal and lateral palate cancers will undergo ipsilateral neck dissections only, while all other patients will undergo bilateral neck dissections. If levels 1 or 5 are involved they will be dissected, otherwise selective neck dissections will be limited to levels 2–4. For patients with positive margins at the primary site at the time of TORS, an attempt can be made at the time of neck dissection to clear the positive margin transorally.

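### The neck-dissection rule for lateral primaries makes no exception for an involved contralateral node, although such patients are eligible (minor)

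*Protocol article*

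**What the plan says.** All references are to the protocol article.

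- **Inclusion criteria.** Eligible nodal stages include "N2 (between 1–3 cm, on either side of the neck", provided imaging shows no extranodal extension. Nothing ties this to the primary subsite, so a tonsil cancer with a contralateral node can be randomised.
- **Neck dissection, opening rule.** "Patients will undergo standard selective neck dissections for the lymph node areas at risk".
- **Neck dissection, rule by primary site.** "Patients with tonsillar, lateral pharyngeal and lateral palate cancers will undergo ipsilateral neck dissections only"; everyone else has both sides dissected. This split covers every patient and depends on the primary site alone.
- **Neck dissection, exception for involvement.** "If levels 1 or 5 are involved they will be dissected". This concerns nodal level. No matching exception concerns side.
- **Table 1.** The row "Gross tumor and nodes" gives 70 Gy in 35 fractions for Arm 1 and N/A for Arm 2.
- **Adjuvant radiotherapy and chemotherapy.** Radiotherapy may be left out when five features are all absent. Nodal disease is one of the five; close margins are not. The list that follows recommends radiotherapy for margins under 2 mm.

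**The concern.** Two instructions in one section conflict for one kind of eligible patient. With a lateral primary and a known contralateral node, the opening rule calls for dissecting the involved side and the site rule excludes it. A surgeon who follows the site rule exactly leaves known disease in place, in an arm whose dose table provides no gross-node dose. A surgeon who dissects the involved side departs from the printed rule. What is at stake is the treatment of a few patients and clarity about what counts as a protocol deviation.

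The lesser point concerns adjuvant radiotherapy. For a patient whose only adverse finding is a close margin, one list permits omission and the next recommends treatment.

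**Working it through.** The article gives no figure to reproduce on this point. The check sets the rules side by side for a worked case and then compares nominal doses.

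**Worked case 1: T1–2 tonsil primary with a 2 cm contralateral node, no extranodal extension on imaging.**

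1. *Eligible?* Yes. The node lies within 1–3 cm and either side is allowed.
2. *Arm 1.* The gross tumor volume takes in "any nodes that are either: 1 cm or more in short axis", as well as nodes that are necrotic, PET-positive or biopsy-proven. Assuming the node meets one of these criteria, it receives 70 Gy in 35 fractions. N1–2 disease also receives concurrent systemic therapy.
3. *Arm 2, surgery.* Tonsil is on the lateral list, so the contralateral side is not dissected. The exception for levels 1 and 5 does not help.
4. *Arm 2, radiotherapy.* The gross-node row is N/A. The 64 Gy volume covers only positive margins and extranodal extension, so it does not apply here. Two possibilities remain:
   - If the contralateral side counts as pathologically positive, for example by biopsy, it belongs to the 60 Gy volume.
   - Otherwise it falls in the low-risk volume: "A lower-risk nodal volume (CTV54) can be defined to include the standard lymphatic drainage sites that have not been dissected". The verb is permissive, but the next sentence is not: once a node is positive, that volume must take in the contralateral neck. The dose is 54 Gy.
5. *Arm 2, systemic therapy.* Required only for positive margins or extracapsular extension, so the contralateral node alone does not trigger it.

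**Nominal dose to that node, compared with Arm 1**

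| Arm 2 volume | Dose | Ratio to 70 Gy | Shortfall |
|---|---|---|---|
| Pathologically positive neck | 60 Gy in 30 | 60/70 = 0.857 | 70 − 60 = 10 Gy (14.3%) |
| Low-risk, undissected neck | 54 Gy in 30 | 54/70 = 0.771 | 70 − 54 = 16 Gy (22.9%) |

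These are nominal totals, with no correction for fraction size or overall time.

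**Signs that this is a drafting slip**

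- The Arm 1 volume rules allow ipsilateral treatment only for lateralised tonsil primaries without nodes, and require the contralateral neck to be treated once a node is positive. The surgical rule in Arm 2 lacks that condition.
- The Arm 2 volume rules foresee pathology that is positive on both sides. Under the site rule, dissection could not show this for a lateral primary.
- The N/A for gross nodes in Arm 2 makes sense only if known nodes are expected to be removed.

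**Worked case 2: pT1–2, pN0, no lymphovascular invasion, 1 mm margin.** None of the five features in the omission list is present, so radiotherapy may be left out. The margin is under 2 mm, so radiotherapy is recommended. Both rules apply to the same patient. Re-resection of a close margin is optional under the TORS section, so such cases can remain.

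**The case against.** The best reply is that the opening rule governs and the site-based sentence only sets a default by expected drainage. On that reading the involved side is dissected and no harm follows. Safeguards support it: patients must be "presented at multidisciplinary tumor board prior to randomization", radiotherapy plans go through quality assurance rounds and central review, and adjuvant treatment follows NCCN guidelines. The article also condenses a fuller protocol that may state the exception.

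Much of this stands. Literal application is unlikely and the number affected is probably small. But the safeguards do not repair the sentence. The radiotherapy reviews concern plans, not the extent of dissection, and in Arm 2 they come after surgery. The article has not left out a detail here; it states a rule that conflicts with another.

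A reader might go further and infer that the node could receive no radiotherapy at all, because an undissected node yields no specimen and the omission list speaks of pathological features. The documents do not support that as a realistic outcome. Nodal disease is one of the features that must be absent before omission, any positive node is an indication for radiotherapy, the protocol recognises biopsy proof of a node without dissection, and a positive node brings the contralateral neck into the 54 Gy volume. A zero dose forms no part of this point.

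On close margins, it is fair to say that the specific recommendation would usually prevail over a permissive clause. The sentence on perineural invasion, which refers to other indications for radiotherapy, also suggests that the indications list is the operative one. The mismatch is real but small.

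**Conclusion.** The point holds as a minor error in a stated treatment rule. Read literally, a known contralateral node with a lateral primary in Arm 2 stays undissected and would generally receive 54 Gy, or 60 Gy if that side is pathologically positive. Arm 1 gives 70 Gy with systemic therapy. The nominal shortfall is 16 Gy (23%) or 10 Gy (14%).

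This rests on three assumptions: the site rule is followed to the letter, the node meets an Arm 1 gross-volume criterion, and a positive node is recognised when Arm 2 radiotherapy is planned. The article does not say how many patients have this presentation; few is a judgement, not a figure.

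A reader might also infer that the trial's comparison or its power is compromised. Nothing in the article supports that: the sample size of 68, the alpha level, the endpoint and the primary t-test are unaffected. The close-margin mismatch is a lesser inconsistency whose intended reading is clear, and its effect cannot be quantified from the document.

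**What to change.** **Neck dissection.** After the clause restricting lateral primaries to the ipsilateral side, add: *unless a contralateral node is clinically or radiologically involved, in which case bilateral neck dissections will be done*. Leave the rule for all other primaries as it is.

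**Adjuvant radiotherapy and chemotherapy.** Add *close margins (<2 mm)* to the features that must be absent before radiotherapy is omitted, so that this list agrees with the recommendation list below it. If margins cleared by re-resection are mentioned, use the same wording for positive and close margins, since the TORS section treats the two alike for re-resection.

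**Cost.** Both changes fit in one amendment with ethics approval. The clinical downside is the morbidity of a second dissected neck side in a few patients. Sample size and analysis do not change.
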